## **Version date:** February 27, 2022

## **Summary of the project**

| Study title | Mainz Immunoadsorption Study in Adults with Post-COVID (IAMPOCO) |
| --- | --- |
| Applic | [name], MD |
| Study location | Main |
| Fund | Third-party funding (Diamed Medizintechnik, Cologne, Germany) |
| Study design/type | Prospective randomized single-blind placebo-controlled study |
| Number of subjects | 40 subjects |
| Study population | Adults recruited from participants in the Gutenberg Post-COVID Study who had at least one positive SARS-CoV-2 PCR test at least 6 months prior to study inclusion, as well as new or persistent symptoms of SARS-CoV-2 infection 3 months after a positive PCR test that have persisted for at least 2 months. |
| Planned start of study | March 8, 2023 |
| Study duration per subject | 4.5 |
| Planned study duration | Recruitment period: 6 months  Duration of the clinical study: 18 months |
| Primary endpoint | Effectiveness of immunoadsorption on symptom burden in patients with post-COVID syndrome as measured by the values of:   - Post-COVID-19 Functional Status Scale (PCFS) - Chalder Fatigue Scale - Montreal Cognitive Assessment (MOCA) - MFI-20 - Bell Score - Strength measurement   And their comparison before and after verum therapy and before and after sham therapy (before therapy cycle 1/after therapy cycle 1 and before therapy cycle 2/after therapy cycle 2) |

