The possible pathomechanisms suspected to be behind these syndromes are diverse. However, the pathogenesis and underlying causes are not yet fully understood.^6^ Similarly, the causes of post-COVID syndrome are still unclear.^4^ Both clinical pictures are thought to involve autoimmune mechanisms triggered by the body's response to infection and sustained by the similarity of the body's own proteins to pathogen components (molecular mimicry).^7In^the context of this autoimmunity, antibodies against the body's own structures may also be formed, such as antinuclear antibodies, which target components of the cell nucleus.^7^ In patients suffering from ME/CFS, antibodies against α- and β-adrenergic receptors and against muscarinic acetylcholine receptors, among others, have been detected.^8^ No correlations between antibody concentrations and the severity of the disease or the clinical picture of ME/CFS could be demonstrated, nor are these antibodies specific or sensitive for ME/CFS.^8, 9^

With the detection of autoantibodies in patients with ME/CFS, forms of therapy that specifically target the formation of autoantibodies have also been investigated. For example, two randomized controlled trials involving 30 and 151 ME/CFS patients investigated B-cell-depleting therapy with the anti-CD-19 antibody rituximab versus placebo. The results showed no significant improvement in fatigue symptoms compared to placebo, although a reduction in B-cell concentration was achieved.^10, 11^ In the primary endpoints (improvement in fatigue symptoms after 3 months and after 24 months), there was no significant difference between placebo and rituximab therapy in either study.^10, 11^

Immunoadsorption is another therapeutic option for reducing the concentration of autoantibodies. In this procedure, the patient's blood is first separated into cellular components and plasma, and then the plasma is passed through adsorbents.^12^ The adsorbents have specific surfaces for binding different classes of immunoglobulins, so that the plasma is then largely purified of immunoglobulins and thus also of autoantibodies and returned to the patient together with the cellular components.^12^ This reduces the concentration of immunoglobulins and thus also the concentration of autoantibodies. ^12, 13^ Immunoadsorption is one of the established treatment options for many antibody-mediated autoimmune diseases.^14^

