## **6. Target parameters**

6.1 Primary endpoints:

Effectiveness of immunoadsorption on symptom burden in patients with post-COVID syndrome measured by the values of:

- Post-COVID-19 functional status scale (PCFS)
- Chalder Fatigue Scale
- Montreal Cognitive Assessment (MOCA)
- MFI-20
- Bell Score
- Strength measurement

and comparison before and after active treatment and before and after sham treatment (before treatment cycle 1/after treatment cycle 1 and before treatment cycle 2/after treatment cycle 2).

6.2 Secondary endpoints:

- Frequency of adverse events under active and sham treatment
- Prevalence of anti-adrenergic and anti-muscarinic autoantibodies in patients with post-COVID syndrome:
  - Proportion of subjects with evidence of anti-α1-adrenoreceptor Abs
  - Proportion of subjects with evidence of anti-α2-adrenergic receptor Abs
  - Proportion of subjects with evidence of anti-β1-adrenoreceptor Abs
  - Proportion of subjects with evidence of anti-β2-adrenergic receptor Abs
  - Proportion of subjects with evidence of anti-β3-adrenoreceptor Abs
  - Proportion of subjects with evidence of anti-M1 acetylcholine receptor Abs
  - Proportion of subjects with evidence of anti-M2 acetylcholine receptor Abs
  - Proportion of subjects with evidence of anti-M3 acetylcholine receptor Abs
  - Proportion of subjects with evidence of anti-M4 acetylcholine receptor Abs
- Concentration of:
  - Anti-α1-adrenoreceptor Abs
  - Anti-α2-adrenoreceptor Abs
  - Anti-β1-adrenoreceptor Abs
  - Anti-β1 adrenoreceptor Abs
  - Anti-β1 adrenoreceptor Abs
  - Anti-M1 acetylcholine receptor Abs
  - Anti-M2 acetylcholine receptor Abs
  - Anti-M3 acetylcholine receptor Abs
  - Anti-M4 acetylcholine receptor Abs

Before and after active and sham treatment (before therapy cycle 1/after therapy cycle 1 and before therapy cycle 2/after therapy cycle 2).

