## 9.6 Total duration of the study

The total duration of the study is set at 24 months. This study duration is based on the fact that 40 participants are to be recruited and then treated. One treatment cycle lasts one week. Each participant receives two treatment cycles, so that two weeks of pure therapy must be calculated per participant. Since the capacity for extracorporeal procedures at the study center is limited, this long period of time is necessary to be able to carry out a sufficient number of therapies. Twenty months are therefore scheduled for the therapy, two months for the necessary preliminary examinations and study inclusion, and two months for the follow-up visits.

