10.2 Burdens and risks associated with participation in the study

- Pain, hematomas, accidental arterial puncture, damage to peripheral nerves during peripheral venous cannulation before each immunoadsorption or sham adsorption, reduction of risk through ultrasound-guided cannulation
- Insertion of a central venous dialysis catheter (Shaldon catheter) if peripheral venous cannulation is not possible, with risk of injury to the carotid artery, bloodstream infections, risk of lung injury with development of pneumothorax Reduction of risks through sterile working practices, ultrasound-guided catheter placement, and the extensive experience of the physicians involved in the study in catheter placement
- Allergic reaction to heparin, adsorbent material, or tubing materials
- Development of heparin-induced thrombocytopenia (HIT) with the development of thromboembolism, a drop in platelet concentration, and the development of bleeding
- Stress caused by two hospital stays of 7 days each

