10.3 Discontinuation criteria

- Participation in the study is voluntary. Patients may withdraw from the study at any time without giving a reason and without any subsequent disadvantage.
- Definition of adverse events (AE): Adverse events are defined as any disturbances in well-being observed during the course of treatment.
- Serious adverse event (SAE): An SAE is life-threatening or fatal. It leads to significant or persistent disability, hospitalization, and includes any significant risk that may harm the patient and is related to the treatment administered.
- Non-serious adverse event (AE): All events that do not fall under the SAE category.

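### Section 10.3 ties adverse events to the course of treatment, so non-serious events between the end of cycle 2 and the 4-week follow-up fall outside the only safety endpoint, and on a narrow reading so do events between the cycles

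*Protocol*

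**What the plan says.** - Section 10.3 (Discontinuation criteria) defines the events: "Adverse events are defined as any disturbances in well-being observed during the course of treatment". The next two bullets define serious events, by consequence and relation to treatment, and non-serious events, as everything that is not serious. Neither gives a time limit of its own.
- Section 6.2 makes these events a secondary endpoint: "Frequency of adverse events under active and sham treatment". The project summary enters safety parameters as not applicable, so this is the only safety outcome.
- Section 9.6 gives the length of treatment: "One treatment cycle lasts one week", and "two weeks of pure therapy must be calculated per participant".
- Section 10.2 lists the risks, among them bloodstream infection from a central catheter and "Development of heparin-induced thrombocytopenia (HIT) with the development of thromboembolism, a drop in platelet concentration, and the development of bleeding". It gives no times of onset.
- The Scientific background describes what the adsorber does: "so that the plasma is then largely purified of immunoglobulins and thus also of autoantibodies".
- Table 5 schedules a follow-up visit at 4 weeks with a medical history interview and a blood sample. Tables 1 and 2 schedule assessments before cycle 2 (vT2). None of these is linked to adverse-event recording.

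**The concern.** The definition decides which events enter the data. An analysis plan can choose how to analyse recorded events, but it cannot recover events that the protocol told staff not to count. In a cross-over with short cycles and a visit four weeks later, a rule tied to treatment leaves part of the observation time uncovered.

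At stake is the completeness of the only safety outcome. The protocol does not say that bloodstream infection, heparin-induced thrombocytopenia with thromboembolism, or any effect of removing immunoglobulins must show itself within the treatment week. An event first noticed after discharge could therefore be left out, or recorded at the discretion of staff who, in this single-blind trial, know the treatment given.

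**Working it through.** **Inputs.** Cycle length of one week and two cycles per participant (section 9.6). Two hospital stays: "Stress caused by two hospital stays of 7 days each" (section 10.2), although the Table 4 caption gives 9 days for cycle 2. Follow-up at 4 weeks (Table 5), taken here as counted from the end of cycle 2. Planned numbers of 2 x 20 (Biometrics). The text does not state the interval between cycles, and the flow charts are not shown; call it g days.

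**Step 1: the plan's own figure.** 2 cycles x 1 week = 2 weeks = 14 days of treatment, as section 9.6 says. With a 9-day second stay it is 7 + 9 = 16 days.

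**Step 2: what each reading of section 10.3 covers (non-serious events).**

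| Period | Narrow: the two cycles | Broad: the whole two-cycle programme |
|---|---|---|
| Cycle 1, 7 days | counted | counted |
| Between cycles, g days | not counted | counted, treatment not assigned |
| Cycle 2, 7 days (9 by the Table 4 caption) | counted | counted |
| End of cycle 2 to follow-up, 4 x 7 = 28 days | not counted | not counted |

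The last row is the same on both readings. The second row depends on the reading, and the protocol does not settle it.

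**Step 3: what the broad reading does to the two treatments.** After the first treatment a participant is observed for g days; after the second, for 0 days. With 20 participants per sequence, all completing both cycles:

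- verum: 20 x g + 20 x 0 = 20g participant-days after a cycle
- sham: 20 x 0 + 20 x g = 20g participant-days after a cycle

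The totals balance, but each participant contributes time after only one of the two treatments, so the within-person comparison is lost for that period. Withdrawal before cycle 2, which the protocol allows, could upset the balance in either direction.

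**Step 4: equal windows instead.** Let w be the smaller of 28 and g. If events are recorded for w days after each cycle, each treatment has 40 x w participant-days when all 40 complete, and every participant contributes to both.

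**Step 5: the serious-event bullet.** It has no time limit, but it follows the general definition and reads as a subtype of it. Whether a late serious event counts depends on which bullet governs. A late non-serious event has no such route.

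**The case against.** The strongest reply is that the course of treatment, in a two-cycle cross-over, naturally means the whole programme. That stands as a possible reading and would bring in the interval between cycles. It does not bring in the 28 days after cycle 2.

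A second reply is that the serious and non-serious bullets have no time limit. This holds in part: late serious treatment-related events may well be reported. The non-serious bullet, however, only divides up the events already defined.

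A third is that blood tests at vT2 and the follow-up interview would bring late problems to light. They would make some visible, so it would be too strong to say that nothing from cycle 1 is known when cycle 2 starts. But the protocol does not turn those findings into recorded adverse events.

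A fourth is that assigning events to treatments and choosing a comparison window belong in an analysis plan, which is not at hand. That is fair, and their absence is not counted as a fault here. The recording period is different, because the protocol itself fixes it.

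Three stronger inferences are tempting, and the document does not support them:

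- **That about 90% of participation is lost.** The summary gives "Study duration per subject | 4.5" without a legible unit. Weeks do not fit, since 14 + 28 = 42 days exceeds 4.5 x 7 = 31.5. If months are assumed, 4.5 x 30.44 = 137 days, and treatment is 14/137 = 10% to 16/137 = 12% of it. But a share of days is not a share of events, the 137 days may include evaluation before the first session, and the figure applies only to the narrow reading.
- **That the comparison is biased towards no difference.** Heparin and venous access are common to both treatments, so missing their late harms lowers both counts. A bias would need late harms specific to immunoglobulin removal, and the protocol lists none.
- **That the protocol lists these harms as delayed.** Section 10.2 gives no onset times and ties nerve damage to the cannulation itself.

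**Conclusion.** The point holds as a defect in a definition that the protocol fixes. On either reading, non-serious events in the 28 days between cycle 2 and follow-up are not adverse events under section 10.3; on the narrow reading the g days between cycles are lost as well. The status of late serious events is unclear. Because this is the only safety endpoint and nothing confines the listed risks or the effects of immunoglobulin removal to the treatment week, the rule can miss harms.

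How many events would be missed, and whether the verum-sham comparison would shift, cannot be worked out from the document. The conclusion assumes that the 4 weeks run from the end of cycle 2. It does not depend on the lost unit of study duration or on whether the second stay is 7 or 9 days. The change should be made, but it does not call the design into question.

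**What to change.** Amend section 10.3 as follows:

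1. Define the recording period as running from the start of the first session of therapy cycle 1 until the follow-up visit.
2. Apply that period to serious and non-serious events alike.
3. Assign an event that begins between the start of a cycle and the start of the next cycle (or the follow-up visit) to that cycle's treatment.
4. Compare verum and sham over an equal window after each cycle: 28 days, or the interval between cycles if that is shorter.
5. Ask about events at the existing vT2 assessment and, in the same words, in the follow-up interview in Table 5.

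Items 3 and 4 could sit in the analysis plan; items 1, 2 and 5 need to be in the protocol. The cost is one amended definition, one attribution rule and one question at two time points already scheduled. The downside is that a few more background events will be recorded under both treatments. No treatment, dose or visit changes.

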| Secondary endpoints | 1. Frequency of adverse events under active and sham treatment  2. Prevalence of anti-adrenergic and anti-muscarinic autoantibodies in patients with post-COVID syndrome:   - Proportion of subjects with evidence of anti-α1-adrenoreceptor AK - Proportion of subjects with evidence of anti-α2-adrenergic receptor antibodies - Proportion of subjects with evidence of anti-β1-adrenoreceptor AK - Proportion of subjects with evidence of anti-β2-adrenoreceptor AK - Proportion of subjects with evidence of anti-β3-adrenoreceptor AK - Proportion of subjects with evidence of anti-M1 acetylcholine receptor AK - Proportion of subjects with evidence of anti-M2 acetylcholine receptor AK - Proportion of subjects with evidence of anti-M3 acetylcholine receptor AK - Proportion of subjects with evidence of anti-M4 acetylcholine receptor AK  1. Concentration of:  - Anti-α1 adrenoreceptor AK - Anti-α2-adrenoreceptor AK - Anti-β1 adrenoreceptor AK - Anti-β1 adrenoreceptor AK - Anti-β1-adrenoreceptor AK - Anti-M1 acetylcholine receptor AK - Anti-M2 acetylcholine receptor AK - Anti-M3 acetylcholine receptor AK - Anti-M4 acetylcholine receptor AK   Before and after treatment with active substance and placebo (before therapy cycle 1/after therapy cycle 1 and before therapy cycle 2/after therapy cycle 2) |
| Safety parameters | Not applicable |

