#### Laboratory tests and collection of biomaterial

During participation in the study, venous blood samples will be taken at various times by nursing staff or doctors trained in blood sampling. The parameters to be determined serve, on the one hand, to find or rule out alternative causes for the symptoms reported in the context of post-COVID syndrome and, on the other hand, to provide explanations for any improvements or worsening of symptoms during or after therapy. Most of the laboratory values for the individual participants are already available at the time of study inclusion from the examinations carried out during their participation in the Gutenberg Long COVID Study. Some parameters must be determined several times during study participation. Table 2 shows which parameters are determined at which point in the study.

In addition, a urine test is planned several times during the study, for which the subjects must provide at least 50 ml of midstream urine.

All analyses of blood and urine samples are performed in a pseudo-anonymous manner by the Central Laboratory of the University Medical Center Mainz.

Saliva samples for determining cortisol concentrations at different times of the day will be collected during an inpatient stay on the day before the first extracorporeal therapy of the respective cycle, as these must be processed promptly.

| Parameters | Time of collection | Material |
| --- | --- | --- |
| Complete blood count | E, vT1, nT1, vT2, nT2 | Serum |
| Sodium concentration | E, vT1, nT1, vT2, nT2 | Plasma |
| Potassium concentration | E, vT1, nT1, vT2, nT2 | Plasma |
| Calcium concentration | E, vT1, nT1, vT2, nT2 | Plasma |
| Phosphate concentration | E, vT1, nT1, vT2, nT2 | Plasma |
| Transferrin saturation | E, vT1, nT1, vT2, nT2 | Serum |
| Ferritin | E, vT1, nT1, vT2, nT2 | Serum |
| C-reactive protein | E, vT1, nT1, vT2, nT2 | Plasma |
| Antinuclear antibodies | E, vT1, nT1, vT2, nT2 | Serum |
| Daily profile of cortisol concentration in saliva | E, vT1, nT1, vT2, nT2 | Saliva |
| Thyroid-stimulating hormone | E, vT1, nT1, vT2, nT2 | Serum |
| 25-hydroxy vitamin D concentration | E | Serum |
| Vitamin B12 concentration | E | Serum |
| Immunoglobulin G concentration | E, vT1, nT1, vT2, nT2 | Serum |
| Antibodies against α-adrenoreceptors of subtypes 1-2 | E, vT1, nT1, vT2, nT2 | Serum |
| Antibodies against β-adrenergic receptors of subtypes 1-3 | E, vT1, nT1, vT2, nT2 | Serum |

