### Medical-technical examinations

- - - 1. Physical examination, anthropometry, and vital signs

Each study participant undergoes a physical examination by a physician, which includes auscultation of the heart and lungs and a clinical examination of the abdomen. The height and weight of each participant are recorded and used to calculate their body mass index.

Vital signs are recorded by medically trained personnel using electronic devices. Resting blood pressure is determined oscillometrically using an upper arm cuff after 5 minutes of physical rest in a sitting position, heart rate is determined using pulse oximetry, body temperature is measured via tympanic measurement with a laser thermometer, and respiratory rate is counted.

The results of the physical examination, anthropometry, and vital signs are taken from the data of the Gutenberg Long COVID Study.

In addition to the measurements of vital signs, which are determined for the collection of study data, heart rate, oxygen saturation, and blood pressure are continuously monitored during each therapy session, both during the active and placebo therapy, or every ten minutes in the case of blood pressure, using electrical devices.

- - - 1. 12-channel ECG

A 12-channel ECG is recorded for each study participant as part of the Gutenberg Long COVID Study. Data from the findings of these 12-channel ECGs will be transferred to the immunoadsorption study, as this could provide clues to the causes of the symptoms experienced by the participants. The rhythm, QT time, ST segment findings, and any block patterns are transferred.

- - - 1. Spirometry

In order to record the lung function of the subjects and to determine the possible influence of the therapy cycles on lung function, as well as to evaluate a possible correlation between the reported dyspnea symptoms and the measured lung function, spirometry will be performed on each participant. Initially, each subject has already undergone spirometry, which was performed during participation in the Gutenberg Long COVID Study. After each therapy cycle, another spirometry test will be performed by the Center for Preventive Cardiology. Parameters for determining obstructive and restrictive ventilation disorders will be measured, as well as the diffusion capacity of the lungs.

- - - 1. Neurological examinations

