| Anthropometry | Yes | E |
| Vital signs (HR, RR, temp., respiratory rate) | no | E, T1, T2 |
| 12-channel ECG | Yes | E |
| Spirometry | Yes | E, nT1, vT2, nT2, F |
| Neurological examination | Yes | E, nT1, vT2, nT2, F |
| Neurocognitive testing | Yes | E, nT1, vT2, nT2, F |
| PCFS score | No | E, nT1, vT2, nT2, F |
| Chalder fatigue scale | no | E, nT1, vT2, nT2, F |
| Bell score | No | E, nT1, vT2, nT2, F |
| MRC score | no | E, nT1, vT2, nT2, F |
| Blood sampling | yes | E, T1, nT1, T2, vT2, nT2, F |
| Urine analysis | Yes | E, nT1, vT2, nT2, F |
| Cranial MRI | yes | E |
| Psychological questionnaires | yes | E, nT1, vT2, nT2, F |

Table2 : Overview of examinations performed, proportion of examinations whose results can be used from the Gutenberg Long COVID study as part of the evaluation examinations, and when the respective examinations are performed. (E = evaluation examinations; T1 = during therapy cycle 1; T2 = during therapy cycle 2; vT1 = before therapy cycle 1; nT1 = after therapy cycle 1; vT2 = before therapy cycle 2; nT2 = after therapy cycle 2, F = follow-up; for most examinations, the evaluation examination is equivalent to the examination before therapy cycle 1).

- 1. Informing participants about examination results

After each examination, the test subjects will receive brief information if there are any relevant examination results. After completion of the study, participants will receive a detailed written report of the findings and an appointment will be offered to discuss the findings.

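### Section 10.3 ties adverse events to impaired well-being alone, so a non-serious, symptomless laboratory abnormality would not count toward the adverse-event endpoint (minor)

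*Protocol*

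**What the plan says.** Section 10.3 of the protocol states: "Adverse events are defined as any disturbances in well-being observed during the course of treatment". It then gives a serious class, which among other things "includes any significant risk that may harm the patient and is related to the treatment administered", and a non-serious class made up of whatever is left over. Section 6.2 and the synopsis both list as a secondary endpoint "Frequency of adverse events under active and sham treatment".

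Section 10.2 names heparin-induced thrombocytopenia as a risk and mentions the platelet fall as one of its features. Heparin is given in both verum and sham cycles (section 9.5; amendments, item 3).

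Table 1 schedules blood count, fibrinogen and immunoglobulin G at evaluation and before and after each cycle. The section on laboratory tests gives the values two purposes: "The parameters to be determined serve, on the one hand, to find or rule out alternative causes for the symptoms reported" and "to provide explanations for any improvements or worsening of symptoms during or after therapy".

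The synopsis row on safety reads "Safety parameters | Not applicable".

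**The concern.** A definition built on well-being leaves out findings that the patient does not notice. The protocol names such a finding as a risk and measures it at suitable times under both treatments, but its definition gives no reason to count it.

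What is at stake is the completeness of one secondary endpoint. If the text does not say whether a symptomless abnormality counts, that will be decided case by case or after the data are in. The study is single-blind, only the subjects are described as blinded, and the protocol does not say who classifies events. A stated criterion removes that choice for laboratory findings.

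**Working it through.** There is no figure in the plan to reproduce. The check sets the definitions against the kinds of event that could occur.

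1. **Bleeding or thromboembolism.** These would be felt or seen. They fall under the general definition and count.
2. **A dangerous platelet fall without symptoms.** It is not a disturbance in well-being, but the serious class "includes any significant risk that may harm the patient and is related to the treatment administered". It may therefore count as a serious event.
3. **A non-serious platelet or fibrinogen fall without symptoms.** It is not a disturbance in well-being and poses no significant risk. The remaining route is the non-serious class, but that line sorts events into serious and non-serious and does not say what an event is. Read literally, the fall is not counted.
4. **The immunoglobulin G fall.** It is not counted either, and should not be. The scientific background describes removal of immunoglobulins as what the treatment does.

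Could another part of the protocol close the gap in case 3? The laboratory section does not. Finding other causes of the reported symptoms, and explaining changes in symptoms, are both tied to symptoms. Nowhere does the protocol make an abnormal laboratory value an adverse event.

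**Are the data there?** Table 1 lists samples before and after each cycle (vT1, nT1, vT2, nT2). The blood-sampling row of Table 2 reads "Blood sampling | yes | E, T1, nT1, T2, vT2, nT2, F", with no vT1, but the note to Table 2 says that for most examinations the evaluation visit (E) stands for the one before cycle 1. A before-and-after comparison is therefore possible in both cycles, with E in place of vT1 where needed.

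**Size.** The protocol gives no rate of symptomless laboratory abnormalities, so the undercount cannot be computed. For scale only: if all 40 subjects (section 8.4) complete both cycles and an assumed share p of cycles has such an abnormality, the number left out per treatment is 40 × p.

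| Assumed p | Left out per treatment |
| --- | --- |
| 1% | 40 × 0.01 = 0.4 |
| 5% | 40 × 0.05 = 2 |
| 10% | 40 × 0.10 = 4 |

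These rates are assumptions and not estimates. They say nothing about a difference between verum and sham.

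**The case against.** The best reply is that the wording is loose rather than exclusionary. The serious class already reaches beyond felt complaints, so the notion of an event may be wider than well-being, and the left-over class could then be read as a catch-all. That reading is possible but strained. The line subdivides adverse events that have just been defined by well-being, and if it were a true catch-all it would conflict with that definition, so the text would still need repair.

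A second reply is that little remains: serious falls may be covered, symptomatic ones are covered, and the values can be recovered from scheduled samples. This stands, and it is why the point is minor. Numerical laboratory limits are also often left to an analysis plan, which may exist. The definition of an adverse event, however, is stated here and governs what is recorded during the study.

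A reader might infer that the definition hides a verum/sham difference. The documents do not support that. The same definition applies in both cycles, heparin is given in both, and no rates by treatment are given. Nor does the single-blind design make this a special problem of bias. Who classifies events matters for every adverse event, and the blood and urine analyses are done by the central laboratory under pseudonyms.

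A reader might also take the synopsis row to mean that safety is not assessed. It does not show that. The adverse-event endpoint stands in the row above, so the entry can mean that there are no further parameters. It is true that "heart rate, oxygen saturation, and blood pressure are continuously monitored during each therapy session, both during the active and placebo therapy", but the same sentence sets this monitoring apart from the vital signs collected as study data.

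Finally, counting every value newly below the laboratory's limit would go too far. The caption of Table 4 says that the before and after samples are drawn during extracorporeal therapy, so a marginal value may reflect the procedure. This objection stands and shapes the fix.

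**Conclusion.** The point holds as a minor one. As written, section 10.3 does not count a non-serious, symptomless laboratory abnormality toward the secondary adverse-event endpoint. This rests on reading the general definition literally and on treating the non-serious class as a subdivision of it.

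The size of the undercount is unknown and cannot be obtained from the protocol. No effect on the verum/sham comparison is shown, no data are lost, and the primary analysis and sample size are untouched. The synopsis entry on safety parameters deserves an editorial remark and no more.

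**What to change.** In section 10.3, define an adverse event as any untoward medical occurrence, including a clinically relevant new or worsened laboratory abnormality by a pre-stated objective criterion applied identically in both cycles.

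- Use the scheduled samples: vT1 (or E where it serves as the value before cycle 1) against nT1, and vT2 against nT2.
- Set the criterion by clinical relevance and not merely by crossing the laboratory's limit, because the samples may be drawn during the procedure.
- Report laboratory events on a separate line, so that the symptomatic count stays visible.
- Describe the immunoglobulin G fall, but do not count it as an adverse event.

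As an editorial correction, replace the synopsis entry with a reference to adverse-event frequency and the laboratory values used for it.

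The cost is one clause and one table row, with no extra visits or patients. No extra samples are needed either, provided that E is accepted where vT1 is not drawn. The downside is a slightly higher adverse-event count.
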